## Abstract

**Background:**

Focal therapy for prostate cancer has been proposed as an alternative treatment to whole-gland therapies in selected men to diminish side effects in localized prostate cancer. As nowadays imaging cannot offer complete prostate cancer disease characterization, multicore systematic biopsies are recommended (transrectal or transperineal). Optical imaging techniques such as confocal laser endomicroscopy and optical coherence tomography allow in vivo, high-resolution imaging. Moreover, they can provide real-time visualization and analysis of tissue and have the potential to offer additive diagnostic information.

**Objective:**

This study has 2 separate primary objectives. The first is to assess the technical feasibility and safety of in vivo focal imaging with confocal laser endomicroscopy and optical coherence tomography. The second is to identify and define characteristics of prostate cancer and normal prostate tissue in confocal laser endomicroscopy and optical coherence tomography imaging by comparing these images with the corresponding histopathology.

**Methods:**

In this prospective, in vivo feasibility study, needle-based confocal laser endomicroscopy and optical coherence tomography imaging will be performed before transperineal template mapping biopsy or radical prostatectomy. First, confocal laser endomicroscopy and optical coherence tomography will be performed in 4 patients (2 for each imaging modality) undergoing transperineal template mapping biopsy to assess the feasibility and safety of confocal laser endomicroscopy and optical coherence tomography. If proven to be safe and feasible, confocal laser endomicroscopy and optical coherence tomography will be performed in 10 patients (5 for each imaging modality) undergoing radical prostatectomy. Confocal laser endomicroscopy and optical coherence tomography images will be analyzed by independent, blinded observers. Confocal laser endomicroscopy– and optical coherence tomography–based qualitative and quantitative characteristics and histopathology will be compared. The study complies with the IDEAL (Idea, Development, Exploration, Assessment, Long-term study) stage 2a recommendations.

**Results:**

At present, the study is enrolling patients and results and outcomes are expected in 2019.

**Conclusions:**

Confocal laser endomicroscopy and optical coherence tomography are promising optical imaging techniques that can visualize and analyze tissue structure, possible tumor grade, and architecture in real time. They can potentially provide real-time, high-resolution microscopic imaging and tissue characteristics of prostate cancer in conjunction with magnetic resonance imaging or transrectal ultrasound fusion-guided biopsy procedures. This study will provide insight into the feasibility and tissue-specific characteristics of confocal laser endomicroscopy and optical coherence tomography for real-time optical analysis of prostate cancer.

**Trial Registration:**

ClinicalTrials.gov NCT03253458; https://clinicaltrials.gov/ct2/show/NCT03253458 (Archived by WebCite at http://www.webcitation.org/6z9owM66B)

**Registered Report Identifier:**

RR1-10.2196/9813

## Introduction

Prostate cancer (PCa) is the leading noncutaneous cancer in men and the third cause of cancer-related death [1]. To date, patients with a clinical suspicion of PCa, based on elevated serum prostate-specific antigen (PSA) and/or suspicious digital rectal examination (DRE), are recommended to undergo transrectal ultrasound (TRUS; +/− multiparametric magnetic resonance imaging, mpMRI)–guided systematic biopsies [2]. This work-up for PCa diagnosis carries some important drawbacks. Due to the heterogeneous nature of PCa, this procedure has a known risk of missing PCa lesions or underestimating PCa aggressiveness, besides overdiagnosis of insignificant lesions [3,4]. In the last decade, the diagnostic pathway for PCa has, therefore, moved more and more into imaging-based targeted biopsies instead of random systematic biopsies. Reliable prostate imaging is key for the reduction of unnecessary biopsies, insignificant PCa detection, increasing detection of significant PCa, reducing the number of cores, and to facilitate monitoring during active surveillance. Moreover, reliable imaging would play a pivotal role in treatment planning, and monitoring of focal treatment for low- to intermediate-risk localized PCa [5-8]. Especially, mpMRI of the prostate has evolved as an increasingly appealing tool in the PCa diagnostic armamentarium and is recommended in men with suspicion of PCa following a negative initial biopsy, and currently, it is even proposed to select patients for biopsies [2,5]. For focal therapy, in which the aim is to target treatment of significant disease with minimal toxicity, accurate disease identification, localization, demarcation, and grading of a lesion are essential. Focal therapy selection with mpMRI-targeted biopsies may be an option in experienced hands, but to date, there is a substantial proportion of false positives in lesions 3/5 or 4/5 scored with the prostate imaging reporting data system (PI-RADS) [9]. Moreover, the assessment of mpMRI-negative areas or the prostate as a whole using a transperineal prostate mapping biopsy using a template-guided approach is recommended [2,10,11]. Transperineal template mapping biopsies (TTMB) are able to sample the prostate at every 5 mm, and coordinates are correlated to the tumor location. Limitations of this procedure are the large numbers of cores needed per prostate, the rate of urinary retentions, and the operating room time with its accompanying hospital admission [12,13]. Moreover, pathologists face a substantial increase in workload with a high number of biopsies, which often turn out to be benign.

Optical imaging technologies offer real-time imaging with excellent spatial and temporal resolution and are easily integrated into the operating room. In conjunction with mpMRI/TRUS-fusion image targeted biopsy, these real-time technologies in a needle-based form could provide valuable information for tissue characteristics. Adding real-time, in vivo diagnostic information of prostate tissue structure and architecture to already known information could improve PCa disease characterization. Optical imaging has the potential to make the diagnostic procedure less invasive, speed up the pathway, and reduce the currently existing workload of histopathological analysis.

Two optical imaging techniques currently used for needle-based optical biopsies are confocal laser endomicroscopy (CLE) and optical coherence tomography (OCT) [14-17]. CLE and OCT differ in background technology and image geometry and, therefore, show different images of the scanned tissue, see Figures 1 and 2.

CLE uses low-power laser bundles in a fiber optic probe, which can be inserted into the lumen of a needle to obtain real-time microscopic images of the tissue that is investigated. Backscattered light, from one specific tissue plane, is focused through a pinhole, whereas the backscattered light from surrounding tissue is rejected. This leads to high-resolution imaging of one specific plane of tissue in focus. The fluorescent light originates from the fluorescent dye nested in the extracellular matrix after topical or intravenous application. The most commonly used fluorescent dye is fluorescein. CLE is under investigation for gastrointestinal, urothelial, and pulmonary diseases, whereas for PCa, so far, only one study on CLE has been reported [14,18-20]. Lopez et al performed CLE during robot-assisted laparoscopic prostatectomy (RALP) in 21 patients to investigate the ability of CLE to assess surgical margins and nerve tissue with promising CLE-based characteristics of prostatic and periprostatic tissue [20]. In addition, no adverse events were reported related to the CLE procedure. However, these authors did not assess the ability to differentiate malignant from benign prostate cells.

OCT is the optical equivalent of ultrasound imaging, based on the backscattering of near-infrared light. Flexible OCT probes, which can be inserted into a needle lumen, enable side looking real-time imaging with an axial resolution up to 10 μm and an effective penetration depth of around 2 mm [21]. Cross-sectional images are generated using an automated pullback system while the probe is rotating a small laser light bundle over the tissue. Within urology, OCT has been applied in evaluating malignancy of bladder, upper urinary tract, kidney, testes, and prostate lesions [22]. In PCa, OCT has been applied for intraoperative identification of neurovascular bundles, surgical margins, and extracapsular extension with the goal to preserve patient’s functional and oncological outcomes [23-26]. A limited number of studies have looked at OCT’s diagnostic role in differentiating benign and malignant microscopic tissue of the prostate gland. Muller et al demonstrated with the use of a histopathologic validation tool that ex vivo needle-based OCT measurements of radical prostatectomy specimens could differentiate between cancer and healthy prostate tissue [27-29]. The quantitative analysis of the OCT signal by means of the attenuation coefficient was significantly higher in malignant compared with benign tissue with an area under the curve ranging from 0.64 to 0.89 depending on the histopathological analysis used [29].

The development of CLE and OCT toward real-time optical biopsies of prostate carcinoma may lead to advances in diagnosis and (focal therapy) treatment. Following phase 2a of the IDEAL criteria [30], we have separated the study protocol into 2 sequential aims with different procedures.

Procedure 1 aims to evaluate the technical feasibility of needle-based in vivo imaging with CLE and OCT in the prostate.

Procedure 2 aims to describe characteristics to be used for PCa detection, which allows us to create an atlas of CLE and OCT characteristics of normal and malignant prostate tissue based on a one-to-one comparison with histology.

**Figure 1 figure1:**
[figure not shown]
Two examples of confocal laser endomicroscopy (CLE) images with Cellvizio AQ-flex 19 probe of ex vivo prostate tissue soaked in fluorescein solution for 2 min.

**Figure 2 figure2:**
[figure not shown]
One b-scan of fixated ex vivo prostate tissue visualized with optical coherence tomography (OCT) with C7-XRtm Imaging System interfaced to a C7 Dragonflytm Imaging Probe (St. Jude Medical, St. Paul, Minnesota, USA).

## Methods

### Study Objectives

The objective of procedure 1 is to assess the technical feasibility and safety of in vivo, needle-based, focal imaging of prostate tissue with CLE and OCT.

Procedure 2 has as primary objective to identify and define characteristics of PCa on CLE and OCT images. The secondary objectives are to correlate CLE and OCT images with histopathology, to develop an in vivo CLE and OCT image atlas of the prostate, and to assess procedure-related adverse events. The atlas will differentiate prostate tissues including benign glands, cystic atrophy, regular atrophy, stroma, inflammation, fat as well as different grades of malignant tissue using the Gleason score. The procedure-related adverse events will be evaluated using the Common Terminology Criteria for Adverse Events.

### Study Design

This study is an investigator-initiated, multicenter, prospective in vivo feasibility study, using in vivo needle-based imaging methods with CLE and OCT. Approval of the local institutional review board (IRB) has been obtained for the study protocol under registry number: NL57326.018.17 on July 7, 2017, and the study was registered on the clinicaltrials.gov database (NCT03253458) on August 18, 2017. Any amendments to the trial protocol will be submitted for review by the IRB. Trial registrations will be updated, and participants will be informed about the risks and benefits of participation both verbally by one of the investigators and in writing in the form of an extensive patient information brochure. Participants will only be included after written informed consent has been obtained. Patients can leave the study at any time for any reason if they wish to do so without any consequences. The investigator can decide to withdraw a subject from the study for urgent (medical) reasons. Patient data will be anonymized and stored in a secure database.

The study design consists of 2 sequential procedures. CLE images are recorded with the AG-Flex 19 fiber optic mini probe-based system (Cellvizio System, Mauna Kea Technologies, Paris, France) with an outer diameter of 0.9 mm, a field of view of 325 µm, and a resolution of 3.5 µm. OCT images are recorded with a small rotating C7 Dragonfly Imaging Probe using the Light Lab OCT system (St. Jude Medical, Saint Paul, Minnesota, USA). Both devices and probes are illustrated in Figure 3.

For CLE imaging, a fluorescent contrast agent is needed to stain the extracellular matrix. Fluorescein (fluorescein sodium, Fresenius Kabi, Zeist, the Netherlands), a nontoxic and commonly used fluorescent dye, will be administered intravenously through an intravenous cannula [31]. Two times a bolus of 2.5 mL of 10% sodium fluorescein will be administered, one bolus per CLE measurement. The probes are transperineally introduced through a 17-gauge needle under ultrasound guidance. CLE images are recorded at a scan rate of 12 frames per second during a push and scan technique after placing the probe in direct contact with prostate tissue.

The OCT probe will be placed with a trocar needle in the prostate tissue under ultrasound guidance. After removal of the trocar needle, the inner part of the probe, the laser lens system is automatically pulled back while it is rotating, which creates a 3D image of the tissue.

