**Figure 3 figure3:**
[figure not shown]
A: Cellvizio CLE system, B: Cellvizio confocal Miniprobe (AG-Flex 19) through the 17-gauge introducer needle, C: St. Jude Lightlab optical coherence tomography (OCT) system, D: St. Jude OCT probe with a 0.9 mm diameter.

In procedure 1, patients scheduled for TTMB will undergo in vivo CLE or OCT imaging, before colocalized biopsy for standard histopathological assessment.

If it is shown in procedure 1 that in vivo CLE and OCT imaging are technically feasible and safe to perform, then procedure 2 will be initiated. In procedure 2, patients scheduled for RALP will undergo in vivo CLE or OCT imaging during surgery, before prostate removal. In general, 2 recordings of 90 s each will be made for the per-patient chosen modality. Recorded CLE and OCT imaging will be analyzed, at a later stage, by blinded independent observers and compared with the corresponding histopathologic evaluation of the prostatectomy specimen. Histopathological analysis is performed according to the standard clinical protocol and will be performed by a uropathologist, blinded for OCT and CLE imaging results. The uropathologist will, next to the standard examination procedure, perform a detailed reporting method; prostate tissue will be analyzed and annotated for various structures (benign glands, cystoid atrophy, regular atrophy, stroma, malignant tissue using the Gleason score, inflammation, and fat) on the whole mount histology slice or biopsies specimens. Histopathology is correlated with CLE and OCT data in a 3D computer environment. Adverse events are registered with a follow-up of 30 days.

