### Population

Patients (aged ≥18 years) who are indicated for a TTMB will be included for study procedure 1. All patients will be recruited in the AMC Hospital (Amsterdam, the Netherlands), and all study procedures will be performed in this institution. A total of 14 patients will be included in this study (Figure 4). Four patients will be included for procedure 1, 2 patients for optical imaging with CLE, and 2 with OCT. For procedure 2, 10 patients scheduled for RALP will be included, 5 of these patients will be imaged by CLE, 5 patients by OCT. Patients will be recruited in the AMC Hospital and VU Medical Center (Amsterdam, the Netherlands), and study procedures will be performed in both institutions. To increase the focal targeting of a PCa lesion, patients included in procedure 2 should have prostate mpMRI data available before the RALP with a visible (>5 mm) and suspect (PI-RADS v2: ≥3) region of interest. The other inclusion and exclusion criteria are listed in Textboxes 1 and 2, respectively. These sample sizes are based on prior publications and comply with the IDEAL 2a recommendation: low number of selected patients [29,30,32].

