##### Confocal Laser Endomicroscopy Measurement Technique

For the CLE measurement, 0.5 mL of fluorescein (2.5% fluorescein diluted in saline) is intravenously injected for contrast. The CLE probe is inserted using a 17-gauge trocar needle. When the CLE is in contact with prostate tissue, the measurement begins; while recording, the probe and needle are pushed from apex to base. During this push and scan technique, the probe stays in contact with the tissue.

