#### Procedure 2: Robot-Assisted Laparoscopic Prostatectomy (10 Patients, 5 Confocal Laser Endomicroscopy Imaging and 5 Optical Coherence Tomography Imaging)

In the operating theater, before the RALP, the CLE or OCT measurements will be obtained in the same fashion as in procedure 1. Dimensions of the prostate will be measured on the ultrasound console. Following marked regions from the mpMRI, the CLE or OCT measurements will be made following the technique described earlier. After measurement, a plastic cannula will be left in the specific trajectory as a localization marker. This marker shows the measurement location necessary for analysis once the prostate has been removed. After the cannula placement, the TRUS-probe and stepper will be removed, and the standard RALP can start. The plastic cannulas will remain in place during the removal of the prostate. Figure 5 shows the flowchart of procedure 2.

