### Benefits and Risks

As the patients included in this study are already scheduled for radical prostatectomy or TTMB, no direct benefit exists. The results of this study may be relevant for patients in the future for PCa diagnosis, grading, and staging. CLE and OCT are promising imaging techniques that in conjunction with the TRUS/mpMRI fusion guided biopsy procedure can provide real-time, high-resolution 3D microscopic imaging and tissue characteristics of PCa.

Previous in vivo studies using CLE or OCT did not report any adverse events, and these modalities are performed by needle guidance with the same diameter or smaller as the standard biopsy needles. In case of a RALP, 2 plastic cannulas will be placed using an intravenous needle. The plastic cannulas will stay in the prostate during the surgery and could, therefore, harbor an increased risk for infection, positive surgical margin rate, or other (unknown) complication during surgery. Standard antibiotic prophylaxis (ciprofloxacin) will be administered 2 h before surgery to reduce the risk of infection. The proposed needle-based imaging techniques also imply a puncture into the prostate and, therefore, have a risk of complications such as bleeding. However, bleeding is believed to be limited as only 2 needles will be placed; complications will be documented and critically analyzed in this safety and feasibility study. Fluorescein is a commonly used fluorescent dye that will be administered intravenously through an intravenous cannula. Previous reports have proven that it is safe and easy to administer [36-38]. Possible side effects include nausea, vomiting, abnormal taste sensations, thrombocytopenia, and allergic reactions. Patients with a known allergic reaction to fluorescein are excluded from participation in this study. Standard care and pathological evaluation as stated by the internal protocols will not be affected in this study. In conclusion, we believe that the burden and risk associated with participation in this study are limited.

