Several studies have provided in vivo images of CLE, but do not show a comparison with histology or an in-depth interpretation of the prostate images [38]. On the basis of histopathology, it is expected that benign prostate tissue differs in extracellular structure compared with malignant prostate tissue. The fluorescein, provided by intravenous injection, gives contrast to the extracellular matrix on the CLE images, which could potentially allow to discriminate between benign and malignant prostate tissue. The described protocol will compare histology and CLE to provide knowledge of visual characteristics on CLE images.

Locating and recording the position of the in vivo measurements is difficult and will be less precise than an ex vivo measuring environment. The in vivo measurement locations will be mapped by ultrasound, and the measurement trajectory will be marked for ex vivo histology comparison. Regardless of this precise measurement mapping, the size and shape of the prostate will change after removal and formaldehyde fixation and could cause potential correlation errors [41]. These changes in dimensions will be recorded by measuring the size of the in vivo prostate by ultrasound and when fixated, to be able to correct for prostate shrinkage. During the comparison of in vivo measurements and ex vivo histopathology, the measurement trajectory will be scaled. The length of the measurement trajectory will be scaled following the shrinkage of the prostate. Shrinkage of tissue over the trajectory is not uniform, but this is in our opinion is the best available option to correct for the shrinkage.

This study is an essential first step for the clinical evaluation of optical imaging in PCa diagnosis. In the clinic, a tool for optical histology could potentially guide a biopsy needle with instant feedback of the region of interest for reliable diagnosis and treatment of PCa.

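### The intravenous fluorescein dose for CLE is stated twice, and the two statements differ 20-fold in mass as written

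*Protocol article*

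**What the plan says.** The protocol article describes fluorescein administration in two places.

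- **Study Design**, which covers the whole study: "Two times a bolus of 2.5 mL of 10% sodium fluorescein will be administered, one bolus per CLE measurement".
- **Confocal Laser Endomicroscopy Measurement Technique**, under Study Procedures: "For the CLE measurement, 0.5 mL of fluorescein (2.5% fluorescein diluted in saline) is intravenously injected for contrast".

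Three other statements bear on how these fit together.

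- Study Design, in the text after Figure 3, sets the number of recordings: "In general, 2 recordings of 90 s each will be made for the per-patient chosen modality".
- The section on procedure 2 says that "the CLE or OCT measurements will be obtained in the same fashion as in procedure 1".
- Benefits and Risks confirms the intravenous route and lists possible side effects, including nausea, vomiting, thrombocytopenia and allergic reactions. It gives no dose.

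**The concern.** Both statements describe the same drug, route, purpose and unit of use (a CLE measurement), yet neither the volume nor the concentration agrees. At least one of them is wrong as written.

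Two things depend on the dose.

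**Safety.** Safety is part of the objective of procedure 1, and procedure-related adverse events are a secondary objective of procedure 2 (Study Objectives). Procedure 2 opens only if procedure 1 is found feasible and safe. For CLE that decision rests on 2 patients. A finding of no harm in 2 patients says little unless the amount of dye they received is known.

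**Image content.** The Discussion states that "The fluorescein, provided by intravenous injection, gives contrast to the extracellular matrix on the CLE images", and the Introduction attributes the fluorescent light in CLE to the dye. The CLE characteristics and the atlas are to be derived from 5 patients in procedure 2, which runs at two institutions. If operators or sites followed different sections, differences in brightness between patients would partly reflect the amount of dye, and 5 patients are too few to separate the two. Another group could not reproduce the imaging conditions from this text.

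**Working it through.** The protocol does not state a mass, so there is no figure of its own to reproduce. The check converts each specification to milligrams.

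**Inputs**

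- Study Design: 2.5 mL at 10%, one bolus per measurement, two boluses.
- CLE measurement technique: 0.5 mL at 2.5%, for the measurement.
- Recordings per patient: 2 (Study Design).
- CLE patients: 2 in procedure 1 and 5 in procedure 2 (Population: "5 of these patients will be imaged by CLE, 5 patients by OCT").
- Assumption: percentages are weight per volume, so 10% = 100 mg/mL and 2.5% = 25 mg/mL. The ratio needs only that both percentages use the same convention.

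**Formula:** mass = volume × concentration.

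| | Study Design | CLE technique | Ratio |
|---|---|---|---|
| Volume | 2.5 mL | 0.5 mL | 5 |
| Concentration | 100 mg/mL | 25 mg/mL | 4 |
| Mass per measurement | 2.5 × 100 = 250 mg | 0.5 × 25 = 12.5 mg | 250 / 12.5 = 20 |
| Two measurements | 500 mg | 25 mg | 20 |

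**Could another reading reconcile them?**

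1. *One dose expressed at two dilutions.* At 25 mg/mL, 250 mg would occupy 250 / 25 = 10 mL, not 0.5 mL.
2. *The second statement means 0.5 mL of the 10% stock, diluted to 2.5%.* That is 0.5 × 100 = 50 mg in 50 / 25 = 2 mL. The ratio is 250 / 50 = 5.
3. *The second statement means one injection per patient.* The per-patient ratio is 500 / 12.5 = 40.
4. *One dose for each procedure.* Study Design describes CLE imaging for the whole study, and procedure 2 is to be measured as procedure 1 was, so the doses cannot be divided this way.

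The readings considered give gaps of 5-, 20- and 40-fold. None gives agreement.

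**Patients affected:** 2 + 5 = 7 of 14. OCT uses no fluorescein, so the other 7 are not affected.

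**The case against.** The strongest reply is that this is a journal article condensing a protocol approved by the review board. Operators may work from that protocol, which may state a single dose. The article therefore shows an error in print. It does not show that patients receive different doses, or that the dose given goes unrecorded. That is correct, and the consequences above are conditional for this reason. It does not remove the contradiction: the article has not left the dose to a fuller document but has stated it twice, incompatibly.

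A second point is that a varying dose need not bias the comparison of benign with malignant tissue. Tissues along one recording share one bolus, so a dose that differed between patients would mainly add between-patient variation. It would bias the tissue comparison only if the tissue mix also differed with dose. CLE evaluation is qualitative, and the protocol plans quantitative analysis for OCT only. This also stands, and the documents do not say how contrast changes with dose, so the effect on the images cannot be sized. The risk remains for any characteristic compared across patients, because 5 patients give no means of separating dose from patient or grade.

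Third, known fluorescein allergy is an exclusion and adverse events are registered for 30 days. These measures protect patients, but they do not tell a reader which exposure the safety result refers to.

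Finally, 20-fold is the literal reading per measurement. It should be quoted as such, with the 5- to 40-fold range beside it.

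**Conclusion.** The concern holds. As written, the two specifications give 250 mg and 12.5 mg of intravenous fluorescein per CLE measurement, a 20-fold difference. The gap is 5-fold on the most conciliatory reading considered and 40-fold per patient if the second statement means a single injection. It affects all 7 CLE patients, half of the study. The masses assume weight-per-volume percentages; the contradiction does not.

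The documents do not establish which dose is correct, whether practice has varied, or how much image contrast would change. The point should nevertheless be corrected as essential, because the dose defines the exposure behind the safety objective and the imaging condition behind the CLE atlas.

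**What to change.** 1. Check both sections against the approved protocol and the pharmacy order to establish the intended dose.
2. State it once, in Study Design or in the CLE technique section: volume in mL, concentration in %, mass in mg per bolus, and number of boluses per patient. Replace the other statement with a cross-reference. If the solution is diluted before injection, give the volume and concentration after dilution.
3. Record the mass actually given for every CLE measurement. Noting the time from injection to recording as well would help in interpreting contrast, although the discrepancy itself does not require it.
4. Recruitment was under way when the article appeared. For any patient already imaged, report which specification was used, and do not pool images across the two without flagging it.

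The cost is a wording correction, or a notification to the review board if the approved text carries the same conflict, plus one extra field on the case report form for the mass given. Sample size, eligibility, histopathology and the OCT analysis are unchanged.
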